### Study aims

The primary aim is to determine the effectiveness of a lifestyle therapy program targeting four components of lifestyle (diet, physical activity, sleep hygiene, and substance use), compared to a psychological therapy program, for reducing depressive symptoms in adults with major depressive disorder or bipolar disorder. The primary outcome is change in depressive symptoms at 8 weeks, immediately post-treatment, as measured by the Montgomery–Åsberg Depression Rating Scale (MADRS). Secondary aims are to (i) determine the cost-effectiveness of the lifestyle program relative to psychological therapy, (ii) examine whether the lifestyle program improves lifestyle behaviours relative to psychological therapy, and (iii) conduct a process evaluation to determine the reach, adoption, effectiveness, implementation, and maintenance of the program beyond the research period using the RE-AIM framework [13].

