### Sample size

A Minimal Clinically Important Difference (MCID) for the MADRS primary outcome measure has been shown to be 1.6–3.0 [16–20], therefore the non-inferiority margin was set at < 1.6.

Power analysis was conducted to analyse the non-inferiority hypothesis of between group mean difference greater than the Minimal Clinically Important Difference. Several assumptions were made including a MCID on the MADRS = 1.6 [16], a Standard Deviation (*sd*) of change in MADRS scores from baseline to week 8 = 3.6 (baseline variance = 4.03) were assumed, resulting in a total sample size of 126. An Intraclass Correlation Coefficient = 0.2 was used to account for variation between therapy groups with an average size of 8 per group. A conservative level of attrition = 20% was further assumed.

Using the formula from Van der Weele et al. [21], the Design EFFect (DEFF) for *n* = 8 participants per therapy group, the final sample was therefore 126*2.4/0.8 = 378 with 189 participants per arm.

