**Outcome measures**														
Depressive symptoms (MADRS)		X	X									X		
Bipolar depression rating scale (BDRS)			X									X		
Depression symptoms (PHQ-9)			X									X	X	X
Anxiety symptoms (GAD-7)			X									X		
Social support (MOS-SSS)			X									X		
Smoking, alcohol and drug use (ASSIST)			X									X		
Self-efficacy (GSE)			X									X		
Sleep difficulties (ISI)			X									X		
Assessment of Quality of Life (AQoL 4D)			X									X		
Health service use			X									X		
HDL, LDL, total cholesterol, triglycerides			X									X		
Fasting blood glucose			X									X		
Gut microbiome composition			X									X		
Body mass index (BMI)			X									X		
Stool consistency (BSFS)			X									X		
Nutrition (DQES v3.2)			X									X		
Physical activity (SIMPAQ and Borg scale)*			X			X	X	X	X	X	X	X		
Session-specific Participant Feedback						X	X	X	X	X	X			

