### Data analyses

A comparison of baseline measures and demographic variables across allocation arms will be conducted to ensure the treatment arms are well balanced. Further, a comparison of drop-out rates across allocation arms will also be carried out and variables associated with drop-out will be identified using binary logistic regression analysis. A three-level hierarchical linear model analysis (or multi-level model analysis) will be conducted for all primary and secondary outcome measures, allowing for correlations within treatment groups (level 3) and individual participants (level 2) and repeated measurements over time (level 1). Changes between baseline and the primary endpoint (8-weeks) (continuous outcomes on the MADRS) will be presented as an Intention-To-Treat (ITT) and Per Protocol analyses with the greatest confidence for non-inferiority occurring when results between analysis sets are concordant. Any demographic variables associated with allocated arm or drop-out rates will be controlled for. Finally, follow-up analyses will be conducted for primary and secondary measures, again using a three-level hierarchical linear model analysis.

Consistent with ICHe9(R1) and the pragmatic approach adopted in this trial, a treatment policy estimand will be applied throughout. Thus, all data regardless of anticipated intercurrent events (e.g., missed assessment sessions, treatment discontinuation) will be analysed. Wherever possible, missing data will be imputed using pattern mixture modelling under the assumption of Missing Not at Random. Sensitivity analyses will be conducted to assess the effect of missing data and differences between ITT and per-protocol populations.

An interim analysis will be conducted following 50% recruitment. The intention of this analysis will be to assess efficacy and futility, along with safety considerations to inform trial cessation.

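### The primary MADRS contrast is a change from baseline with no stated adjustment for baseline MADRS, which forgoes a modest gain in precision

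*Protocol article*

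**What the plan says.** All of this is in the protocol article.

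- **Study aims** defines the outcome as a change: "The primary outcome is change in depressive symptoms at 8 weeks, immediately post-treatment".
- **Data analyses** reports it in the same form: "Changes between baseline and the primary endpoint (8-weeks) (continuous outcomes on the MADRS) will be presented as an Intention-To-Treat (ITT) and Per Protocol analyses". The model is a three-level hierarchical one, "allowing for correlations within treatment groups (level 3) and individual participants (level 2) and repeated measurements over time (level 1").
- **Data analyses** gives one rule for covariates: "Any demographic variables associated with allocated arm or drop-out rates will be controlled for". It also plans a balance check, "A comparison of baseline measures and demographic variables across allocation arms will be conducted to ensure the treatment arms are well balanced", but ties no adjustment to what that check shows for MADRS.
- **Sample size** works from the spread of the change score: "a Standard Deviation (*sd*) of change in MADRS scores from baseline to week 8 = 3.6 (baseline variance = 4.03) were assumed".
- **Table 2** schedules MADRS at enrolment, baseline and week 8 only. **Blinding and randomisation** puts the baseline assessment before randomisation, so a pre-randomisation value is available.

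**The concern.** Baseline MADRS is not a demographic variable, so the stated covariate rule does not reach it. Having baseline among the repeated outcomes does not by itself supply the adjustment. If each arm has its own baseline mean, the arm-by-time term is a comparison of change scores. A change score fixes the slope of week 8 on baseline at 1. Where the true slope differs from 1, the interval is wider than the collected data allow, and part of any chance baseline difference stays in the estimate.

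The non-inferiority conclusion rests on one confidence limit set against 1.6 points, so both effects matter a little. The same model serves all secondary outcomes, many of which also have a baseline value.

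**Working it through.** **Inputs.** From Sample size: margin 1.6, SD of change 3.6, baseline figure 4.03, ICC 0.2, 8 per group, 20% attrition, totals 126 and 378. From Study sample: entry requires MADRS of at least 20. Not given there: alpha, power, the week-8 SD and the baseline to week-8 correlation.

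**1. The plan's own figure.** n per arm = 2 × (1.645 + 0.842)² × 3.6² / 1.6² = 62.6, so 63 per arm and 126 in total. Design effect = 1 + 7 × 0.2 = 2.4, and 126 × 2.4 / 0.8 = 378. Both totals reproduce. One-sided 5% with 80% power is inferred: one-sided 2.5% with 80% gives 160, one-sided 5% with 90% gives 174, and one-sided 2.5% with 90% gives 214.

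**2. What the contrast is.** In one simulated complete data set, a mixed model with a participant intercept and separate baseline means gave an arm-by-time estimate of 0.0595, identical to the raw difference in mean change. Constraining the baseline means to be equal gave -0.245, as did regression of week 8 on arm and baseline.

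**3. Slope and adjusted variance.** Let V = 3.6² = 12.96, s0 = baseline SD and s1 = week-8 SD. Then slope b = (s1² + s0² - V) / (2 s0²), and adjusted variance Va = V - (1 - b)² s0². With s0 = s1 = 4.03, b = 19.52 / 32.48 = 0.60 and Va = 10.37, a ratio of 0.80.

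**4. Power.** Baseline MADRS is taken not to explain the therapy-group variance, so that stays at 0.2 × 12.96 = 2.592. Analysed per arm: 189 × 0.8 = 151.2. Variance of the contrast = 2 × (Va + 7 × 2.592) / 151.2. For the change score this is 2 × 31.104 / 151.2 = 0.411, SE 0.641, and power at one-sided 5% is Φ(1.6/0.641 - 1.645) = 80.2%. With adjustment, taking 4.03 as the baseline SD:

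| Assumed week-8 SD | Slope b | Va / V | Power | Gain (points) |
|---|---|---|---|---|
| 4.03 | 0.60 | 0.80 | about 83% | about 3 |
| 4.5 | 0.72 | 0.90 | 81.6% | 1.4 |
| 5.0 | 0.87 | 0.98 | 80.5% | 0.3 |
| 5.4 | 1.00 | 1.00 | 80.2% | 0 |
| 6.0 | 1.21 | 0.945 | 81.0% | 0.8 |

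A simulation of the first row with 6 per group gave a variance ratio of 0.90, matching (10.37 + 5 × 2.592) / (12.96 + 5 × 2.592) = 23.33 / 25.92 = 0.90.

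**5. If 4.03 is literally a variance.** Equal spread at week 8 would need a correlation of 1 - 12.96 / (2 × 4.03) = -0.61, which is implausible. Dropping equal spread, slopes of 0.4 to 0.8 give power of 81.9% down to 80.4%, with group variance held fixed.

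**6. Chance imbalance.** With 4.03 as an SD and 189 per arm, the SE of the baseline difference is 4.03 × √(2/189) = 0.41, and 1.96 SE is 0.81. At slope 0.60 the change contrast shifts by 0.40 × 0.81 = 0.32 points, about 20% of the margin. At a week-8 SD of 5.0 the shift is 0.13 × 0.81 = 0.11. In simulation at slope 0.6 the change contrast moved -0.40 per point of imbalance and the adjusted contrast 0.00.

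**The case against.** The strongest reply is that Data analyses lists the levels of the model and not its fixed effects. It never says that the contrast is unadjusted or that the arms have separate baseline means, and the covariate sentence does not say that nothing else will enter. The same three-level model with a common baseline mean would already give the adjusted result, and an analysis plan that is not shown may specify it. This stands in part: one cannot assert that the trial will run an unadjusted analysis. But the common-mean constraint is a special specification that the text does not state. The ordinary reading of a reported change, with a trial sized on the SD of change, is the unadjusted contrast.

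The objection on size stands in full. The slope of 0.6 needs 4.03 reread as an SD and the same SD at week 8. The entry floor of 20 narrows the spread at entry and does not apply at week 8, so equal SDs are doubtful.

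Three stronger readings are tempting and are not supported:

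- **That power would rise to about 87%.** This applies the 2.4 design effect to the reduced variance (SE = √(2 × 10.37 × 2.4 / 151.2) = 0.574), as if baseline MADRS also explained variation between therapy groups.
- **That the whole baseline imbalance stays in the estimate.** Only (1 - slope) of it does. At a slope below 1 the change score over-corrects, in the opposite direction to the imbalance.
- **That the primary analysis is biased or underpowered.** The change contrast is unbiased over randomisations, its interval allows for chance imbalance, and the sample size was built on its own SD.

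**Conclusion.** The point holds as an efficiency and prespecification improvement. As described, the primary contrast most naturally reads as an unadjusted difference in change, although a pre-randomisation MADRS is collected and adjusting for it costs almost nothing. At best, under equal SDs of 4.03, individual-level variance falls by about 20% and power rises by about 3 points at one-sided 5%. The gain could be close to nil, depending on a week-8 SD that the article does not give. These figures assume the inferred alpha and power, the plan's ICC and attrition, and therapy-group variance unaffected by baseline. The article contains no wrong result on this point. The 4.03 label is a separate matter of clarity in Sample size and does not itself show an analysis error.

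**What to change.** In Data analyses, state that the primary between-arm contrast in week-8 MADRS is adjusted for baseline MADRS whatever imbalance is observed. Either enter baseline MADRS as a covariate, or keep it as a repeated outcome and constrain the arms to a common baseline mean in the three-level model. The second form also keeps participants who have only a baseline value. Say the same for each secondary outcome measured at baseline. If the analysis plan already specifies one of these forms, align the protocol text with it.

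The cost is one sentence before unblinding and, for the covariate form, one model degree of freedom. No new data are needed, the sample size need not change, and the unadjusted change can still be reported descriptively. Separately, state in Sample size whether 4.03 is a variance or an SD.

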### Economic evaluation

A within-trial economic analysis will be conducted from health sector and partial societal perspectives by collecting information on intervention costs, the cost of other healthcare resources used by participants during the trial period, and lost productivity. Health sector costs will include the cost of delivering each intervention, calculated through a micro-costing method, in addition to the cost of additional health services used during the trial period. Partial societal costs will include health sector costs plus the costs of lost productivity. Standard Australian unit costs (i.e., Pharmaceutical Benefits Schedule) will be applied to health service use and the average Australian wage rate plus 25% overhead costs will be used to value lost work time, known as the Human Capital Approach. Differences in total costs from health sector and partial societal perspectives will be compared with differences from multiple outcomes including quality adjusted life years (QALYs) calculated from AQoL-4D utility values [51], and the primary outcome of MADRS between groups. The non-inferiority trial design is likely to result in non-significant differences between groups on costs and mental health outcomes. We anticipate differences between arms on secondary outcomes, such as lipid and blood glucose levels. Economic modelling to extrapolate from these intermediate outcomes to final outcomes will be considered to understand HARMON-E’s cost-effectiveness in the longer term.

### Data management

All participant details including contact details, medical history, clinical interview information, primary and secondary outcome data, and session notes are collected using the Research Electronic Data Capture (REDCap) [52] database. REDCap is hosted by Deakin University and collected data are stored securely on Deakin’s Research Data Store (RDS) on password protected servers. Access to REDCap is password protected, and study staff have restricted access to specific participant data depending on their role and blinding status. All videoconferencing recordings, including clinical interviews, baseline and follow-up data collection interviews, and session recordings are encrypted and stored on Deakin’s RDS. Stool samples are stored at Microba facilities prior to conducting microbial DNA sequencing. All data collected or generated by Microba are stored and managed in a cloud database using Google Cloud Platform (GCP) cloud service, which is protected using GCP security services to provide high levels of data confidentiality, integrity and availability. Blood samples are analysed by a private pathology laboratory (Sonic Healthcare Australia Ltd) and results are uploaded in real time to their portal which is password protected and accessible only by specific study staff members.

### Ethics, integrity, and dissemination

Ethics approval for this study was granted by the Human Research Ethics Committees of Barwon Health (22/48) and Deakin University (2022 − 273). This study is conducted in accordance with the National Health and Medical Research Council National Statement on Ethical Conduct in Human Research (2023) and the Note for Guidance on Good Clinical Practice (CPMP/ICH-135/95). Information pertaining to participant confidentiality, informed consent, and data access have been included in the Participant Information and Consent Form. Raw data will be made available for transparency as per NHMRC requirements for publicly funded data and made available with appropriate ethical investigator approval via the Health Studies Australian National Data Asset (HeSANDA) platform. Important protocol modifications will be communicated to trial staff and ANZCTR via email by the trial coordinator, and reconsenting of participants will be conducted by the trial coordinator via email. Results will be reported using the Consolidated Standards of Reporting Trials (CONSORT) statement [53] using extensions for non-inferiority design and non-pharmacological interventions.

## Discussion

In recent decades, few major treatment advances have been made for individuals living with clinical mood disorders such as unipolar and bipolar depression [54]. This need is exacerbated by an increase in consumer need which has resulted in lengthy waitlists and other access issues for psychological treatments [55]. While a growing body of evidence supports the efficacy of lifestyle therapies for mild to moderate depressive symptoms and their integration into clinical guidelines [8], their uptake as a first-line treatment for adults with mood disorders has been slow. One reason may be the lack of definitive evidence confirming their equivalence with psychological treatment. The HARMON-E trial therefore seeks to address this critical gap. Should lifestyle therapy prove non-inferior to psychological therapy in this population with respect to clinical and cost outcomes, it has the potential to be employed as an interim or alternative approach to alleviate the depressive symptoms of major depressive disorder or bipolar affective disorder. The HARMON-E trial will also provide important data about secondary outcomes of health and wellbeing such as the role of anxiety, sleep quality, aspects of diet quality, physical activity, the relationship between cardiovascular markers, and mechanisms involving the gut microbiome composition of lifestyle-based treatments for Australian adults with clinical depression or bipolar affective disorder.

## Data Availability

Raw data will be made available for transparency as per NHMRC requirements for publicly funded data and made available with appropriate ethical investigator approval.

## Abbreviations

ANZCTR: Australia and New Zealand Clinical Trials Register
RCT: Randomised Controlled Trial
CBT: Cognitive Behavioural Therapy
CALM: Curbing Anxiety and depression using Lifestyle Medicine
IRGT: Individually randomised group treatment
MAGNET: Mental Health Australia General Clinical Trials Network
MADRS: Montgomery–Åsberg Depression Rating Scale
SCID: Structured Clinical Interview for DSM Disorders
GP: General Practice
PHQ-9: Patient Health Questionnaire-9
DQES: Dietary Questionnaire for Epidemiological Studies
SIGMA: Structured Interview Guide for the MADRS
DASS-10: Depression Anxiety Stress Scale – 10
MedDRA: Medical Dictionary for Regulatory Activities
DSMB: Data Safety Monitoring Board
HREC: Human Research Ethics Committee
SIMPAQ: : Simple Physical Activity Questionnaire
ASSIST: Alcohol, Smoking and Substance Involvement Screening Test
ISI: Insomnia Severity Index
CBT-SUITS: CBT Suitability Scale
ITT: Intention-To-Treat
QALYs: Quality Adjusted Life Years
REDCap: Research Electronic Data Capture
GCP: Google Cloud Platform
HeSANDA: Health Studies Australian National Data Asset
CONSORT: Consolidated Standards of Reporting Trials
